# Efficacy and safety of heparin for sepsis-induced disseminated intravascular coagulation (HepSIC): study protocol for a multicenter randomized controlled trial

**DOI:** 10.1186/s13063-023-07853-5

**Published:** 2024-01-02

**Keywords:** Sepsis, Disseminated intravascular coagulation, Heparin, Randomized controlled trial

## Abstract

**Background:**

Disseminated intravascular coagulation (DIC) occurs in 30–50% of septic patients and contributes to high mortality in the intensive care unit (ICU). However, there are few proven interventions for coagulation disorder management in sepsis. Experimental and clinical data have demonstrated that sepsis could benefit from unfractionated heparin (UFH) treatment. To date, there are no large multicenter trials to determine the safety and efficacy of UFH in septic patients with suspected DIC.

**Methods:**

A multicenter, double-blinded, placebo-controlled randomized trial is designed to recruit 600 patients who met sepsis 3.0 criteria and suspected DIC. Participants will be randomized (1:1) to receive UFH or saline via continuous intravenous administration for 7 days within 6 h of enrolment. The primary outcome is ICU mortality. The secondary outcome includes 28-day all-cause mortality, the improvement of Sequential Organ Failure Assessment scores, and the incidence of major hemorrhage. Investigators, participants, and statisticians will be blinded to the allocation.

**Discussion:**

The HepSIC trial is to evaluate the efficacy and safety of UFH on sepsis-related DIC across different areas of China. The small dosage of UFH administration would offer a new potential approach for treating sepsis-related coagulation disorders.

**Ethics and dissemination:**

Ethical approval was granted by all the ethics committees of 20 participant centers. Results will be disseminated via peer-reviewed publications and presented at conferences.

**Trial registration:**

ClinicalTrials.gov NCT02654561. Registered on 13 January 2016.

**Supplementary Information:**

The online version contains supplementary material available at 10.1186/s13063-023-07853-5.

## Background

Sepsis is a life-threatening organ dysfunction caused by dysregulated host responses [1]. Over 48 million people become septic globally each year, with 11 million dying from the disease, representing nearly 20% of all deaths in the world [2]. A total of 30–50% of septic patients suffer from overt disseminated intravascular coagulation (DIC), which contributes to increased mortality in these patients [3, 4].

The release of proinflammatory factors promotes the activation of the coagulation system. Coagulation activation and endothelial injury contribute to clot formation [5, 6]. In turn, the procoagulant status amplifies the inflammatory response, leading to adverse outcomes of sepsis. Of note, sepsis induces the loss of some crucial anticoagulants, such as protein C, antithrombin (AT), and thrombomodulin (TM) [7, 8]. Therefore, the rationale of some anticoagulant therapy is to replenish these downregulated anticoagulants. Clinical evidence about the efficacy of anticoagulation therapy in sepsis remains insufficient. Although recombinant human activated protein C (rhAPC) has been withdrawn from the market, the PROWESS study demonstrated that rhAPC showed a survival benefit in severely septic patients, especially in a subpopulation of overt DIC patients [9]. However, the KyberSept trial demonstrated that high-dose AT III administration had no survival benefit with an increased risk of hemorrhage in severe sepsis or septic shock patients [10]. A randomized controlled trial showed that recombinant thrombomodulin (rhTM) had an increasing trend in survival in sepsis with suspected sepsis-associated DIC [11]. Recently, a meta-analysis of randomized controlled trials suggested that the survival benefit of anticoagulants was observed only in the sepsis with DIC population [12]. Although the SCARLET trial did not show a survival benefit of rhTM among patients with sepsis-associated coagulopathy [13], a post hoc analysis demonstrated that patients with higher thrombin generation markers had lower mortality with the administration of rhTM [14]. Therefore, septic patients with coagulation disorders could benefit from suitable anticoagulation therapy.

However, these replenishment treatments are only suitable for specific subpopulations, and the expense of these medicines is dramatically too high to afford for middle-low income countries. In contrast, unfractionated heparin (UFH), which is less than 1 dollar per ampoule, does not simply supplement what sepsis patients have depleted. Emerging evidence suggests that UFH exerts anti-inflammatory and immunomodulatory properties and protects the endothelial glycocalyx from shedding in addition to its well-known anticoagulant effects [15–17]. Several clinical studies and meta-analyses have demonstrated that heparin may decrease 28-day mortality, while reports on safety outcomes, including the occurrence of bleeding, are insufficient [18–20]. Jaimes et al. reported no survival benefit of UFH in a single-center randomized clinical trial. However, the patients in this study were suspected of sepsis and not patients with coagulation disorder [21]. Additionally, these clinical trials were conducted with small sample sizes in a single center, limiting the evidence of potential benefit in patients with more severe sepsis with coagulopathy.

Therefore, more robust clinical evidence is warranted to evaluate the efficacy and safety of UFH in septic patients with coagulation disorders. Here, we designed a multicenter, randomized controlled trial (RCT) to determine whether the early administration of UFH is efficacious and safe in the treatment of septic patients with suspected DIC in the ICU.

## Methods and trial design

### Study design

The HepSIC study is a multicenter, double-blind, randomized, placebo-controlled trial. The study protocol was approved by the Research and Ethics Committee of the First Affiliated Hospital of China Medical University ([2015]2015-113-2, Shenyang, China). Participants will be allocated randomly to two arms at a 1:1 ratio: the heparin group and the control group. The control group will receive saline only, while the heparin group will receive continuous intravenous UFH administration within 6 h of enrollment for 7 consecutive days. Blinding will be maintained for researchers, participants, and statisticians during the entire study. The study protocol is summarized in a flow chart (Fig. 1). The study protocol follows the Standard Protocol Items: Recommendations for Interventional Trials statement recommendations (Supplemental Fig. 1).

**Fig. 1 Fig1:**
[figure not shown]
The flow chart of the HepSIC study. DIC, disseminated intravascular coagulation. ICU, intensive care unit; SOFA, Sequential Organ Failure Assessment

### Study participants

Participant enrollment is currently ongoing from all the ICUs of 20 hospitals in China. The 20 ICUs are from 20 university hospitals integrating clinical care, scientific research, and teaching across 11 provinces in Northeast China, Northwest China, Southwest China, and East China (see Supplemental Fig. 2 for the participating hospitals). Patients who meet the inclusion criteria and no exclusion criteria at randomization and sign the informed consent forms will be enrolled in the study. The consent form includes the collection and use of participant data and biological specimens. Enrolment must be completed within 12 h after patients are admitted to the ICU. The study period is planned from April 2018 to December 2024.

### Inclusion criteria

Participants will simultaneously meet the following criteria:Patients aged ≥18Diagnosed as sepsis according to the criteria of sepsis 3.0 (The Third International Consensus Definition for Sepsis and Septic Shock) [1]Suspected DIC was assessed with modified ISTH criteria based on platelet count, prothrombin time, and fibrin/fibrinogen degradation products (Table 1).

**Table 1 Tab1:** Modified disseminated intravascular coagulation algorithm

Variable (units)	Value	Points
Platelet count (× 10^9^/L)	≥100	0
	50–99 or >30% decrease within 24 h	1
	<50 or >50% decrease within 24 h	2
Prothrombin time prolongation (s)	<3	0
	3–6	1
	>6	2
D-dimer (μg/mL)	<2	0
	2–8	2
	>8	3
Total needed for study entry		≥4

### Exclusion criteria

Patients will be excluded if they fulfill any of the exclusion criteria.Pregnant or lactating women.Patients with a history of allergy to heparin.Significant hemorrhage or high risk of bleeding, includingIn the acute phase of trauma or active bleedingHistory of severe brain injury, intracranial surgery or stroke, cerebral aneurysm, arteriovenous malformation within 3 monthsA history of congenital hemorrhage (e.g., hemophilia)Underlying fulminant hepatitis, decompensated cirrhosis, or other severe liver diseasesUse of the following medicine:Heparin and heparin analogs (e.g., low molecular weight heparin, dalteparin, tinzaparin) within 12 h before treatmentWarfarin treatment within 7 days and abnormal INR valueThrombolytics within 72 h prior to study dosingOther anticoagulant drugs, including factor Xa inhibitors (e.g., apixaban, rivaroxaban, edoxaban) and direct inhibitor IIa (e.g., dabigatran)Patients with an expected ICU stay of less than 48 h.Cardiopulmonary resuscitation within 7 days prior to enrollment.Participating in other clinical trials in the previous 30 days.Irreversible diseases, such as the late stage of malignant tumors or the terminal stage of other diseases.

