### Criteria for exiting or suspending the trial

Infusion is to be stopped if there is major or life-threatening bleeding, such as intracranial bleeding, gastrointestinal hemorrhage, or severe nosebleeds. If there are some signs of mild bleeding, such as coffee-like stomach contents, mild gum, or skin mucosa bleeding, the physician should closely monitor and judge according to the actual situation.Infusion was suspended 2 h before major surgery and resumed 12 h after the surgery.If the patient at high risk for thrombosis events, such as venous thromboembolism or acute myocardial infarction, must be treated with anticoagulation therapy, the trial needs to be stopped.If there is an unexplained decline of 50% or greater in platelet counts, especially onset between day 5 and 10 after treatment, or the patient meets the 4Ts scoring system for heparin-induced thrombocytopenia (HIT) diagnosis [22], or a positive test of platelet serotonin-release assay (SRA)

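### The exclusion criteria do not name heparin-induced thrombocytopenia, so a patient who already meets the protocol's own HIT condition for exit can be randomised to heparin

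*Protocol article*

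**What the plan says.** **Entry.** The Exclusion criteria section of the protocol article is itemised, with example drugs and washout times. Three items bear on heparin or its substitutes:

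- "Patients with a history of allergy to heparin";
- in the list of excluded drugs, heparin and "heparin analogs (e.g., low molecular weight heparin, dalteparin, tinzaparin) within 12 h before" treatment;
- other anticoagulants, with factor Xa inhibitors and direct thrombin inhibitors as examples.

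HIT, the 4Ts score and the SRA do not appear. Under Study participants, a patient who meets the inclusion criteria, has none of the exclusions at randomisation and consents is enrolled. The same section says: "Enrolment must be completed within 12 h after patients are admitted to the ICU".

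**Exit.** Criteria for exiting or suspending the trial gives three HIT conditions as alternatives: "an unexplained decline of 50% or greater in platelet counts", with emphasis on onset between days 5 and 10; "the patient meets the 4Ts scoring system for heparin-induced thrombocytopenia (HIT) diagnosis"; or a positive SRA.

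**Rationale.** The section on risks says that the exclusion criteria remove patients at greater potential risk. The Discussion names two main concerns, major haemorrhage and HIT, and promises close monitoring of coagulation and bleeding signs.

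**The concern.** The protocol treats HIT as a diagnosis in its own right, with its own score and assay, but uses it only in the exit rules and not at the point of entry. Haemorrhage, the other main concern, has a detailed block of exclusions. HIT has at most the allergy item, which sites would have to interpret.

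What is at stake is patient safety. A patient with suspected HIT could be allocated to a 7-day heparin infusion under the written rules. Platelet counts on days 1, 2, 3, 5 and 7, together with the exit rule, would limit the length of exposure, but they are no barrier to randomisation. Detection during treatment is also harder than usual. The platelet condition requires an unexplained fall, which is difficult to judge in patients enrolled for suspected DIC, and the treating doctors and nurses are blinded to whether the infusion contains heparin.

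**Working it through.** The plan gives no figure on this point, so the check is to take one patient through the written rules.

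**Step 1. The test patient.** A septic adult meets the Table 1 threshold, received heparin that stopped more than 12 hours before study treatment, is on no other anticoagulant, and already has a qualifying 4Ts score or a positive SRA.

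| Written rule | Does it exclude this patient? |
|---|---|
| Heparin allergy | Arguably for past HIT; not clearly for suspected HIT |
| Heparin within 12 h before treatment | No, exposure ended before the window |
| Other anticoagulants | No, none in use |
| Remaining exclusions | None refers to HIT |
| Enrolment rule (Study participants) | Enrols, as no exclusion is clearly met |
| Exit rule, 4Ts or SRA | Met, but this is not an entry rule |

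**Step 2. How far back the 12-hour rule reaches.** Enrolment may take up to 12 h from ICU admission (Study participants), and the infusion starts within 6 h of enrolment (Interventions). The latest start is therefore 12 + 6 = 18 h after admission. At that timing, even heparin stopped 18 − 12 = 6 h after ICU admission falls just at the edge of the window. Heparin given on a ward and stopped at or before admission falls outside it.

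**Step 3. When the exit rule can act.** The reference to days after treatment belongs to the platelet-fall condition only. The 4Ts and SRA conditions carry no start time. A site could therefore apply them between enrolment and the first dose. Even so, the patient has by then been randomised.

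**Step 4. Table 1, as context only.** The points are platelets 0/1/2, prothrombin time (PT) 0/1/2 and D-dimer 0/2/3; the row "Total needed for study entry" requires at least 4. Two platelet points go to "<50 or >50% decrease within 24 h". There are 3 × 3 = 9 combinations of PT and D-dimer points. Those that qualify, as (PT, D-dimer), are:

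- 0 platelet points: (1,3), (2,2), (2,3), so 3 of 9;
- 1 platelet point: these plus (0,3), (1,2), so 5 of 9;
- 2 platelet points: these plus (0,2), (2,0), so 7 of 9.

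Platelets can supply 2 of the 4 points and never reach the threshold alone. A rapid fall or a low count due to HIT can thus help a patient qualify. These counts are table cells, not patients, and they are the same for any cause of a low platelet count. A slow fall that ends at 100 × 10⁹/L or above scores 0.

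**Step 5. Number of patients.** The article gives no rate of prior heparin exposure or of suspected HIT, so no estimate is possible. If k such patients were randomised, about k/2 would receive heparin under 1:1 allocation.

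**The case against.** The case on the other side has several parts.

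- **Allergy may include HIT.** A site may well read a history of heparin allergy to include past HIT, and a clinician and a researcher assess every candidate. This stands for past HIT, so it would go too far to infer that the protocol admits such patients. It does not stand clearly for suspected, unconfirmed HIT.
- **Other exclusions narrow the gap.** A patient moved from heparin to an excluded alternative anticoagulant is already out, and so is one who had heparin within the 12-hour window. This stands and makes the exposed group smaller. It leaves the patient in Step 1.
- **The exit rule might act before the first dose.** A reader might infer that it applies only once treatment has begun. The text does not say that for the 4Ts and SRA conditions, so a heparin dose is possible but not certain. Randomisation of an unsuitable patient remains.
- **Table 1 is not evidence about HIT.** A reader might infer that the score selects HIT patients because the exit rule uses a platelet fall of similar size. The documents do not support this. Low platelets are an intended part of a DIC score, Table 1 counts a percentage fall only within 24 h, and the exit rule has no such window and requires that the fall be unexplained.
- **The article condenses a fuller protocol.** True, but the article prints an itemised list and handles HIT explicitly elsewhere. The objection is to how the printed criteria fit together.

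**Conclusion.** The point holds as a gap in patient safety. On the printed rules, a patient who already meets the 4Ts or SRA condition for exit can be randomised to heparin if prior heparin ended before the 12-hour window and no alternative anticoagulant is in use.

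The size cannot be computed and is probably small. The Discussion says that heparin prophylaxis is not routine in China unless the thrombosis risk is high, and about half of any such patients would receive saline. The conclusion assumes that the printed exclusion list is the one in force and that at least some sites would not read heparin allergy as reaching suspected HIT. Confidence is medium.

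Nothing here shows an effect on the primary outcome, the power or the bias of the treatment comparison, and none should be inferred. The change is worth making because it is cheap and concerns a harm that the protocol itself singles out; it does not put the trial's validity in doubt.

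**What to change.** Widen the heparin-allergy exclusion so that it also covers known, past or suspected HIT, defined as a qualifying 4Ts score or a positive SRA already on record. Apply the 4Ts score at screening to patients with heparin exposure within a look-back period that the sponsor sets; the article gives no basis for choosing its length. Do not require a new SRA, because enrolment must be complete within 12 h of ICU admission. The exit criteria and Table 1 need no change.

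The cost is one longer exclusion item, one screening question about prior heparin, and a 4Ts score for the few patients who answer yes. Routine blood tests are already scheduled at D0. The change needs approval by the competent authority and the ethics committees and will lose a few patients at screening. It protects only patients not yet enrolled, and recruitment was expected to finish by 31 December 2024. No sample-size or analysis figure changes.

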### Risks, AEs, and informed consent

The protocol is designed to ensure the safety of participants. On the one hand, the dose of unfractionated heparin is moderate for critically ill patients. We calculated the dose of UFH or placebo according to the body weight of each participant, and UFH was administered continuously intravenously at 100 U/kg/24 h (no more than 12,500 U per 24 h). On the other hand, patients with greater potential risk were excluded based on exclusion criteria. Of note, adverse events (AEs) and serious adverse events (SAEs) will be observed and recorded during the 28 days of study from enrollment in accordance with the practice guidelines issued by the National Medical Products Administration of the People’s Republic of China. Investigators will evaluate the relationship between events and the intervention and report the AEs and SAEs to the central ethics committee and the data and safety monitoring board.

### Recruitment

All potential participants are approached by a clinician and a researcher to assess eligibility, provide research information, and obtain informed consent. Participants will be informed of the study purpose, procedures, benefits, and risks and will be given adequate time to consult and consider participation. If the participants cannot sign the consent form, a legally authorized representative will do it on their behalf. The consent process will comply with the guidelines outlined in the Helsinki Declaration and the Good Clinical Practice International Coordinating Committee.

Our research team will manage and monitor the trial progress of the 20 participating centers through our created website, which ensures adequate participant enrolment. During the study period, the eligible patients will be enrolled based on predetermined inclusion and exclusion criteria. The screening logs will be maintained on the website to document reasons for excluding candidates.

### Randomization and allocation concealment

There are 20 participant ICUs with 20 investigators. The eligible participants who meet the inclusion criteria and provide informed consent will be randomized using a software-generated randomization number. Each ICU is assigned an independent, random numeric table by the center primary investigator. There are equal numbers of 1 and 2, which represent the control group (sterile saline) and the heparin group (UFH), respectively. Once an eligible participant has enrolled, the independent drug administrators will obtain group information from the assigned table according to the chronological order of recruitment and assign the study drugs to the nurses for administration.

### Interventions

The participants in the heparin group will receive unfractionated heparin (0.9% saline 48 ml + heparin 2 ml) via continuous intravenous infusion for 7 days. The total dose for a 24-h period was less than 12,500 international units (1 ampule) in the heparin group. The heparin ampules (12,500 U per 2 ml) were manufactured by Shanghai No. 1 Biochemistry Company. The other participants in the placebo group will only receive 50 ml of 0.9% saline via intravenous administration. The method and speed of infusion were identical to those of the heparin group. The study drugs will be commenced within 6 h of enrollment for a 7-day period. Participants in the two groups will receive standard care from the attending physician according to the International Guidelines for Management of Sepsis and Septic Shock [1]. Ulinastatin, Xuebijing, and other anticoagulation drugs were not allowed during the study period. Regional citrate anticoagulation is strongly recommended for continuous renal replacement treatment.

### Blinding

An independent drug administrator (commonly a clinical research nurse) in each center will be in charge of preparing the placebo or heparin. The 50 ml transparent syringes were used for drug administration for both groups to ensure an identical appearance. Procedures for administration are identical and will be performed by the nurses in charge of each patient’s treatment. The independent drug administrator will receive group information based on the random numeric table when the available participant enrolls. Once the assignment is known, the drug administrator—who is the only person for whom the link between the sequential ID and the drug is available—instructed a research assistant to adhere the label with the ID to the appropriate syringe containing UFH or saline. The participants, investigators, clinical doctors, and nurses will be blinded to the study drug assignment except for the drug administrator.

### Criteria for exiting or suspending the trial

Infusion is to be stopped if there is major or life-threatening bleeding, such as intracranial bleeding, gastrointestinal hemorrhage, or severe nosebleeds. If there are some signs of mild bleeding, such as coffee-like stomach contents, mild gum, or skin mucosa bleeding, the physician should closely monitor and judge according to the actual situation.Infusion was suspended 2 h before major surgery and resumed 12 h after the surgery.If the patient at high risk for thrombosis events, such as venous thromboembolism or acute myocardial infarction, must be treated with anticoagulation therapy, the trial needs to be stopped.If there is an unexplained decline of 50% or greater in platelet counts, especially onset between day 5 and 10 after treatment, or the patient meets the 4Ts scoring system for heparin-induced thrombocytopenia (HIT) diagnosis [22], or a positive test of platelet serotonin-release assay (SRA)

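### The 12-hour hold after major surgery covers only a resumed infusion; a patient enrolled less than 6 hours after non-cranial surgery must get the first dose inside those hours unless excluded by judgement

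*Protocol article*

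**What the plan says.** Four parts of the protocol article bear on the point.

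- **Hold around surgery** (Criteria for exiting or suspending the trial): "Infusion was suspended 2 h before major surgery and resumed 12 h after the surgery". Suspending and resuming presuppose an infusion that has already begun.
- **Start of study drug** (Interventions; the Study design section gives the same limit): "The study drugs will be commenced within 6 h of enrollment for a 7-day period".
- **Entry window** (Study participants): "Enrolment must be completed within 12 h after patients are admitted to the ICU".
- **Exclusions** (Exclusion criteria): "Patients will be excluded if they fulfill any of the exclusion criteria". One criterion is "Significant hemorrhage or high risk of bleeding", followed by listed items. The only item that names surgery is "severe brain injury, intracranial surgery or stroke, cerebral aneurysm" and related conditions, with a look-back of 3 months.

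The article gives no minimum interval between a completed non-cranial operation and the first dose.

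**The concern.** The sponsor judged that study drug should stay off for 12 h after major surgery and fixed that interval as a number of hours. The same postoperative hours are open at first start, for the same drug and daily dose. Both entry limits also push towards an early start, and the enrolment limit runs from ICU arrival. A patient who comes to the ICU straight from theatre is therefore likely to be considered for enrolment during those very hours.

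The stake is bleeding in patients randomised to heparin. The Risks, AEs, and informed consent section relies on the entry rules here, saying that "patients with greater potential risk were excluded based on exclusion criteria", and the Discussion names major hemorrhage as one of two main concerns. If the only safeguard at first dose is individual judgement, 20 ICUs may handle the same postoperative patient differently.

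**Working it through.** The plan states no figure for the interval from surgery to first dose, so there is none to reproduce. The check adds up the stated time limits and then reads the exclusion list against them.

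**Inputs.** Times are in hours from ICU admission.

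- s = end of surgery (negative if before admission). The values below are illustrative.
- e = enrolment, with e ≤ 12 (Study participants).
- d = first infusion, with e ≤ d ≤ e + 6 (Interventions).
- Hold at restart = 12 h after surgery (Criteria for exiting or suspending the trial).

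**Step 1: the whole window.** The first dose may fall anywhere from 0 to 12 + 6 = 18 h after ICU admission. If surgery ends at admission (s = 0), that range contains all 12 h of the hold.

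**Step 2: by time from surgery to enrolment.** Let t = e − s. The latest compliant start is t + 6 hours after surgery.

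- t < 6: t + 6 < 12, so every compliant start is inside the hold. At t = 1 the latest start is 7 h, and 12 − 7 = 5 h inside.
- 6 ≤ t < 12: a start inside the hold is permitted but can be avoided.
- t ≥ 12: no conflict.

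**Step 3: by end of surgery relative to admission.** A gap of at least 12 h needs e + 6 − s ≥ 12, that is e ≥ s + 6. With e ≤ 12 this is possible only if s ≤ 6. The longest possible gap is 18 − s.

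| Surgery ends (s) | Earliest enrolment that allows a 12-h gap | Longest gap, 18 − s |
|---|---|---|
| −4 h | 2 h | 22 h |
| 0 h | 6 h | 18 h |
| +4 h | 10 h | 14 h |
| +6 h | 12 h | 12 h |
| +8 h | none | 10 h (2 h short) |
| +10 h | none | 8 h (4 h short) |
| +12 h | none | 6 h (6 h short) |

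For surgery ending more than 6 h after admission, no choice of enrolment time meets the interval. Only exclusion avoids an early start.

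**Step 4: the exclusion list.** It has six timed look-backs: 3 months (intracranial and related conditions), 12 h (heparin and analogs), 7 days (warfarin), 72 h (thrombolytics), 7 days (resuscitation) and 30 days (other trials). The heparin and thrombolytic periods are counted back from study treatment, so the article does state rules tied to the first dose. None concerns non-cranial surgery. What remains is the general bleeding-risk criterion, which has no postoperative time limit.

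**Step 5: who enters.** In Table 1 the row "Total needed for study entry" requires at least 4 points, and D-dimer gives at most 3. Every entrant therefore has at least 4 − 3 = 1 point from low or falling platelets or a prolonged prothrombin time. This holds for all participants and is not specific to surgery.

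**The case against.** The strongest reply is that the exclusions already deal with this. The bleeding-risk criterion is mandatory, and its listed items are introduced as examples, so the absence of non-cranial surgery does not admit such patients. Someone a few hours out of major surgery with suspected DIC is an obvious candidate for exclusion. This stands in part: an early start is not inevitable. But the criterion gives no hour count, whereas at restart the sponsor did not leave the matter to judgement.

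Second, the article condenses a fuller protocol, and a postoperative start rule could sit there. That is possible, which is why confirmation comes first. The article does, however, state the hold, both entry windows and a detailed exclusion list, and the gap arises from how these stated rules combine.

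Third, the two situations differ. A restart patient received study infusion until 2 h before surgery, whereas a first-dose patient must have had no heparin for 12 h before treatment. The article also gives no reason for choosing 12 h, and it describes the dose (100 U/kg/24 h, capped at 12,500 U) as moderate or relatively low. This limits the weight of the point. It does not explain the difference in rules, because by restart the earlier infusion has been off for at least 2 + 12 = 14 h plus the operation itself.

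A reader might infer that the protocol contradicts itself, or that starting before 12 h is known to be unsafe. The documents support neither. The hold is silent on first doses and does not conflict with them, and 12 h is the sponsor's own interval, not a demonstrated threshold.

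**Conclusion.** The point holds as a modest gap in a safety rule. On the rules shown, a patient enrolled less than 6 h after non-cranial major surgery, and not excluded by judgement, must start study drug inside hours that are barred at restart. If surgery ended more than 6 h after ICU admission, no permitted enrolment time avoids this.

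The conclusion assumes that the hold means what its wording says, that the 6-h start limit is followed, and that protocol version 1.3 contains no first-dose rule. The article does not say how many patients are affected, and the number may be small. The cases with no compliant enrolment time need an operation after ICU arrival followed by enrolment in the few hours left.

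A reader might also infer that the treatment comparison is compromised. It is not: each ICU's randomisation table holds equal numbers of both assignments, so the gap applies to both arms alike. The matter is patient safety and consistent practice across centres.

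**What to change.** First confirm whether version 1.3 already has a rule for the first dose after surgery. If it does not, amend Interventions and Criteria for exiting or suspending the trial as follows.

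- No study infusion, first or resumed, starts earlier than 12 h after the end of major surgery.
- Where surgery ended no later than 6 h after ICU admission, defer randomisation to at least 6 h after surgery. The first dose can then fall at 12 h or later within the existing 6-h window. At exactly 6 h the only compliant start is at 12 h, so slightly later randomisation is easier where the enrolment limit leaves room.
- Where surgery ended later than that, exclude the patient under the bleeding-risk criterion.

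The 6-h start window should not be extended instead. With surgery ending at +8, +10 or +12 h and randomisation at 12 h, the first dose would fall at 20, 22 or 24 h after admission. That is 8, 10 or 12 h after randomisation, which breaks the start rule and leaves randomised patients untreated meanwhile.

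The costs are small. Some patients start later, against the aim of early treatment, but still no later than 12 + 6 = 18 h after ICU admission. A few are not enrolled. The amendment needs approval and reaches only late entrants: from publication (2 January 2024) to the planned end of recruitment (31 December 2024) is 364 of 2,455 days since 12 April 2018, or 364/2,455 = 14.8% of calendar time.
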